**Fig. 2 Fig2:**
[figure not shown]
Participant flow diagram

### Recruitment process and informed consent

All available lower secondary level school PE teachers in the city will participate in the teacher-training phase of the study, irrespective of their participation, as the city Education Department has accepted the teacher-training phase to be part of PE teachers’ regular in-service training. We will recruit PE teachers and their students for the study via established links with schools and with support from the Education Department. Initial contact will be made with the head teacher of the school provided with details of the study aims and methods and the commitment required by the school. Once head teacher has consented their school to participate in the study, eligible teachers from each school will be invited to participate and provided with information on the study, and the benefits and requirements of participation, and given the opportunity to ask questions. Teachers agreeing to participate to the study will complete an opt-in informed consent form. Students of the PE teachers will be recruited to the study by referral from their teacher. Invitation letters, study information, and opt-out consent forms, with the exception of opt-in consent form for participation in the accelorometry component of the study measures, will be sent to eligible students’ parents or legal guardians via the schools’ online administration and communication software or via email or post. Students whose parents or guardians decline to give consent for their child to participate in the study will be exempted, and will be provided with alternative activities while participating students complete study measures at data collection time points.

### Procedure and data collection methods

The pre-trial baseline data collection will be scheduled for the third week after the beginning of the 2018–2019 school year. The following data will be collected: questionnaires administered to participating teachers and students comprising self-report measures, a one-week physical activity surveillance for participating students using accelerometers, and audio recordings of a selected PE class of each participating PE teacher. At pre-trial, all consenting teachers and students will complete a questionnaire containing demographic, psychological, and behavioural measures. Audio recordings of participating teachers’ classes will also take place during the baseline data collection. Physical activity behaviour will be collected from a subsample of students from the intervention and wait-list control groups using accelerometers for the week after the pre-trial data collection occasion. In addition, parents or legal guardians of participating students will complete self-report measures of demographic information, provision of autonomy support towards out-of-school physical activity, parental affection, and parental control they provide for their children at the baseline data collection.

Pre-trial data collection will be followed, consecutively, by the teacher training and implementation phases of the trial. In the teacher training phase, teachers allocated to the intervention group will receive the autonomy-support training program and teachers allocated to the wait-list control group will receive control education program over the same period. The completion of the training program will be followed by a 1 month implementation phase. In this phase, teachers in the intervention group will apply the techniques they learned in the training program in their regular PE classes.

Following the implementation phase, a post-trial data collection occasion will be scheduled. Data collection will comprise administration of measures identical to those at pre-trial with the exception of the baseline measures of behavioural automaticity, grit, self-discipline, parental affection, parental control, parental autonomy support and demographic measures. Accelerometer data and audio recordings of teachers’ lessons will also be collected from the same subsample of students and teachers, respectively. Follow-up data collection occasions are scheduled for one-, three-, and six-months post-trial. Accelerometer data from the subsample of students and audio recordings of teachers’ lessons will not be collected on the one-month follow up occasion. All assessments will be completed at the three- and six-month follow up data collection occasions, identical to the post-trial data collection occasion. Immediately after the three-month follow up data collection occasion, the wait-list control group will receive the autonomy-support training program. Post-trial and one-month follow up assessments will be conducted for teachers and students from this group, using identical measures as those administered in the intervention group (Fig. 3). Retention of participants will be maximized through pro-active email and telephone communication with school teachers who will provide access to students. Where collection of data on any given collection occasion is prevented due to unforeseen circumstances, we will negotiate an alternative occasion for the data collection as close as possible to the scheduled occasion.

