**Fig. 1 Fig1:**
[figure not shown]
Theoretical framework: Trans-contextual model

The trans-contextual model provides a theoretical framework for developing interventions in educational contexts such as school PE to promote motivation toward, and actual participation in, related activities such as physical activity outside of school. The model implies that strategies aimed at fostering autonomous motivation will promote in-school and out-of-school autonomous motivation toward physical activity, and promote adaptive beliefs and intentions toward out-of-school physical activity and actual physical activity participation. These proposed effects are supported by research demonstrating the trans-contextual effects and confirming the relevant mechanisms involved [10]. The most effective means to support autonomous motivation in school is for teachers to display autonomy-supportive behaviours during PE lessons. Consistent with the model, effects of interventions aimed at promoting autonomy support in students on out-of-school physical activity is expected to be mediated by autonomous motivation in both contexts, beliefs, and intentions. Together, these mediators provide a demonstration of how the intervention functions in promoting physical activity behaviour. In other words, it provides a framework on *how* the intervention works.

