#### Primary outcome variable

The primary outcome measure is students’ post -intervention participation in out-of-school physical activity at the pre-trial, post-trial, one-, three and 6 month follow-up data collection occasions. Physical activity participation will be measured using the short form of the International Physical Activity Questionnaire, IPAQ [42], which will be modified to make explicit reference to out-of-school physical activity. The IPAQ comprises four items recording the frequency (number of days) and duration (hours) of participation in moderate and vigorous physical activity, walking, and sitting over the past 7 days. The physical activity score for moderate and vigorous physical activity and walking is calculated based on norms and expressed in MET-minutes per week. A score for total physical activity in out-of-school contexts is provided by the sum of the duration and frequency of vigorous, moderate and light physical activity scores. The IPAQ has acceptable concurrent validity and reliability indices [43].

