#### Secondary outcome variables

Physical activity behaviour. A subsample of participants (approx. 120) from representative school classes covering grades 7–9 will have their physical activity participation measured using accelerometry. The purpose of this secondary measure is to provide concurrent validity and comparison data to support the IPAQ used as the primary outcome measure.^2^ Participants will wear the accelerometers (Hookie AM 20) for seven consecutive days after each data collection occasions at pre-trial, post-trial, and at the three-, and six-month follow up data collection occasions. These accelerometers have been shown to be valid and reliable in as a measure of physical activity in previous research [2]. Participants will be also asked to complete a short diary of their daily in-school and out-of-school physical activities for the period during which they wear the accelerometer. Data will provide duration participants spent in sedentary, light, moderate, and vigorous intensity physical activity per day. Diary data will be used to identify duration of physical activity on in-school and out-of-school contexts. It will also provide a measure of total energy expenditure in each context. For the purposes of the current study, we will compute total time spent in light, moderate, or vigorous physical activity and total energy expenditure in out-of-school contexts as criterion measure to test the concurrent validity of the IPAQ measure in each participant. The accelerometry data will be included only for those participants who have provided valid accelerometer data for a minimum of 3 days.

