#### Mediating variables

All students will complete a battery of self-report measures of psychological variables based on the trans-contextual model. These factors are expected to reflect the mechanisms by which the intervention affects change in the primary outcome consistent with the model.

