### Data analysis

Multilevel structural equation modelling using the Mplus, v. 8.0 software [59] will be used to test our hypotheses. All analyses will be performed using intention-to-treat analysis and supplemented by per-protocol analyses for all planned outcome variables [60]. Where data is missing for the psychological variables, we will impute missing values using linear interpolation if the data is confirmed missing completely at random. We expect to have data on our primary and secondary outcome measures, as well as mediating measures, at pre-trial and at the allotted follow-up occasions after the delivery of the intervention (post-trial, and at the one-, three-, and six-month follow up data collection occasions after the implementation period). We also expect to have self-report data on parenting from students and their parents or guardians at pre-trial. Student data will be nested within school and teacher/class, and therefore variance in outcome variables may be attributable to school-level and class-level variation as well as variation between students attributable to the intervention itself. Effects of the intervention on study outcomes can be interpreted at the student level after controlling for school- and class-level effects. Our longitudinal design enables also the examination of potential trajectories in the development of outcome variables. We will test the model at each of the follow-up time points with students’ out-of-school physical activity as the primary dependent variable, the intervention condition as a dummy-coded independent variable (1 = intervention group; 0 = control group), and the psychological variables (perceived autonomy support from teachers, autonomous motivation in PE and out-of-school physical activity, attitudes, subjective norms, perceived behavioural control, intentions), as simultaneous predictors. We will statistically control for each of model variables from the previous time point using the standardized residual scores.

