Although school PE has been identified as an important existing network in which messages and interventions promoting out-of-school physical activity participation could be promulgated, interventions to promote out-of-school physical activity through school PE are rare and these studies often only have limited follow-up periods of behavioural outcomes. For example, a previous study [63] demonstrated the effectiveness of a PE delivered intervention aimed at promoting physical activity participation in high school students. However, the study adopted a relatively brief intervention, relied exclusively on self-reported physical activity measures, and only adopted a relatively short term follow-up of students’ behaviour. Our proposed intervention will advance this research by developing a comprehensive autonomy support training program with an associated set of training materials, use accelerometry to verify self-report measures of physical activity, and conduct a longer-term follow up of intervention effects.

One of the key strengths of the current study is the theoretical basis and the provision to test the mechanisms of effectiveness of the intervention. The current intervention is based on the trans-contextual model [10], which provides a clear basis for the mechanisms of the proposed intervention effects. Specifically, we expect the autonomy-supportive intervention delivered by PE teachers to lead to changes in students’ autonomous motivation in school and outside of school, and their beliefs and intentions toward physical activity outside of school. We will test the effects of the proposed intervention on these theory-based constructs as secondary outcomes in the current intervention. Furthermore, because we plan to collect long-term follow up data we will be able to ascertain whether changes in the psychological constructs as a result of the intervention are maintained over time. The current study is the first to specifically design an intervention using this model and to test the theory-based mechanisms of intervention effects.

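### Mediators and activity are reported by the same student on the same occasion, and no device-based check is planned for the mediator-to-activity paths that are to be read as mechanism

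*Protocol article*

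**What the plan says.** All references are to the protocol article.

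- **Outcome.** Under Primary outcome variable: "Physical activity participation will be measured using the short form of the International Physical Activity Questionnaire, IPAQ". It is adapted to out-of-school activity and covers the past seven days.
- **Mediators.** Under Mediating variables: "All students will complete a battery of self-report measures of psychological variables based on the trans-contextual model".
- **Same occasion.** Under Procedure and data collection methods, at pre-trial "all consenting teachers and students will complete a questionnaire containing demographic, psychological, and behavioural measures". For post-trial, "Data collection will comprise administration of measures identical to those at pre-trial", apart from a list of baseline-only scales that includes none of the mediators.
- **Model.** Under Data analysis, out-of-school activity is modelled at each follow-up on condition and seven constructs entered together: "perceived autonomy support from teachers, autonomous motivation in PE and out-of-school physical activity, attitudes, subjective norms, perceived behavioural control, intentions". Each model variable is adjusted for its value at the previous occasion through standardized residual scores.
- **Interpretation.** In the theory section, below Fig. 1: "Together, these mediators provide a demonstration of how the intervention functions in promoting physical activity behaviour". The Discussion lists showing how the intervention works as contribution (ii).
- **Device.** About 120 students wear accelerometers for seven days after the pre-trial, post-trial, three-month and six-month occasions. Under Secondary outcome variables: "The purpose of this secondary measure is to provide concurrent validity and comparison data to support the IPAQ used as the primary outcome measure". The device is not named as an outcome of the mechanism model.

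**The concern.** A student who answers favourably on a given day tends to score higher on both the mediators and reported activity. That produces a positive association between the two with no link to actual activity, and it does so even when both arms report in the same way. If training also raises reported motivation, a biased mediator-to-activity path completes an apparent mechanism.

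Timing adds to this. The IPAQ looks back seven days, while the attitude, control and intention items refer to the coming month. At any one occasion, the activity being predicted therefore comes before the answers that are meant to predict it.

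What is at stake is the mechanism claim. The Discussion criticises an earlier study because it "relied exclusively on self-reported physical activity measures". The mediator-to-activity analysis as written relies on self-report in the same way.

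**Working it through.** **The plan's own figures.** The Sample size section requires 286 analysed students and allows for 40% attrition: 286 / (1 − 0.40) = 476.7, given as 476. The 286 cannot be rebuilt because the model's degrees of freedom are not stated. It is used below only as the analysed n.

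**1. What the previous-occasion adjustment achieves.** This was simulated with two occasions, n = 286, true activity unrelated to all seven mediators, and one style factor acting on all eight scores. Assumptions: mediator intercorrelation 0.4, true-score stability 0.6, individual-level regression without clustering, 2,000 runs per cell. The table gives the rejection rate of the joint seven-mediator test (nominal 5%) with both sides residualised on the previous occasion.

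| Style share of variance | Stability 0.5 | 0.7 | 0.9 | 1.0 |
|---|---|---|---|---|
| 10% | 45% | 22% | 10% | – |
| 20% | 98% | 78% | 25% | 8% |

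With no style the rate is 5.2%. A fully stable style is almost removed. A style that shifts between occasions is not.

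**2. Effect on the planned simultaneous model.** Let λ be the loading of occasion-specific style on every score after adjustment. The documents give no value, so λ = 0.3 and 0.4 are assumed. Variances are standardised, the mediator intercorrelation before style is 0.4, and there is no true link to activity.

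- Spurious mediator–activity correlation: r = λ², which is 0.09 and 0.16.
- Mediator intercorrelation with style included: ρ = 0.4(1 − λ²) + λ², which is 0.454 and 0.496.
- Joint R² = 7r² / (1 + 6ρ) = 0.0567/3.724 = 0.015 and 0.1792/3.976 = 0.045.
- Noncentrality = 286·R²/(1 − R²) = 4.4 and 13.5. On 7 and 277 degrees of freedom the joint test rejects in 27% and 76% of trials. Simulation gives about 25% and 76%. With no style, simulation gave 4% to 7% in repeat runs.
- One given path: coefficient r/(1 + 6ρ) = 0.024 and 0.040; standard error √[(1 − R²)·VIF/277], with VIF 1.61 and 1.74, = 0.076 and 0.077; ratio 0.32 and 0.52. The chance of a significantly positive result is 5% and 7%. Simulation gives about 6% and 7%, against 2% with no style.
- Both links significant for one given mediator, if training raises each mediator by 0.3 SD: about 4% and 5%.
- At least one of the seven paths significantly positive: about 32% and 46%. This is already 17% with no style, so much of it is multiplicity.

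**3. What the device subsample can show.** The smallest correlation detectable with 80% power (two-sided 5%) is tanh[(1.96 + 0.84)/√(n − 3)]. For n = 120 it is about 0.25. After 40% attrition n = 120 × 0.6 = 72, and it is about 0.33. Both are for one occasion.

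**The case against.** Three defences have force.

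- **The plan has safeguards.** The residual scores deal with trait-like response style, as step 1 shows. The Discussion also presents accelerometry as a means of verifying self-report. The first defence is only partial unless style is nearly constant between occasions. The second checks the IPAQ against the device. It does not show that the mediator paths persist when activity is measured by a different source.
- **The size is unknown.** The loadings are assumptions. One common loading is applied to the IPAQ, which asks for days and hours, and to seven-point rating scales, where style may act differently. This stands, and the rates are illustrations only.
- **A condensed article may leave sensitivity models to a fuller plan.** That is fair as to detail. However, the article itself fixes the self-report model, the mechanism reading and the validation-only role of the device.

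A reader might infer that any single mediator would be falsely declared in a third to four-fifths of trials. Rates of about 34% and 79% (24% and 58% for both links) do arise, but only when one mediator is entered alone. The article plans simultaneous entry, so the documents do not support that reading.

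**Conclusion.** The point holds in limited form. Activity and mediators share source and occasion, and neither the residual scores nor the device in its stated role protects the mediator-to-activity paths from occasion-specific shared reporting. Those paths can be biased upward.

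In the planned model the effect shows mainly in the joint test: about 25% and 76% false rejection at assumed loadings of 0.3 and 0.4. Any one given path is little affected (about 6% and 7%). These figures assume n = 286, one common loading, and neither clustering nor latent variables.

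Two stronger inferences are not supported. First, the trial's main hypothesis is not undermined: the overall difference in activity between arms does not depend on the mediator paths. Second, shared style cannot produce a mediated effect by itself when both arms report alike, because a real rise in reported mediators under training is also needed.

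**What to change.** In Data analysis, add a sensitivity analysis that repeats the mediator-to-activity model in the subsample, with accelerometer-measured out-of-school activity as the outcome and the device occasions pooled. The device is worn in the seven days after the questionnaire, so it is a different source and in the right time order. Because control schools are trained after the three-month occasion, let the condition term differ by occasion.

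Report estimates and intervals beside the IPAQ-based paths. Describe a path seen only with the IPAQ as a self-report association not confirmed by device, and not as a demonstrated mechanism.

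The cost is analysis wording only, with no new data. The downside is precision: with 72 to 120 students many paths will stay unconfirmed. A non-significant device result should therefore not be read as evidence against a path, and no rule requiring the two estimates to agree in size should be set.

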## Methods

### Trial design

The study will adopt a cluster-randomized, wait-list control, single-arm intervention design with randomization by school. The trial comprises two phases: a teacher-training phase and an implementation phase. The teacher-training phase will comprise a two-week, 12-h training program in which secondary school teachers will receive the autonomy-support training program developed for the present study. The teacher-training program will be preceded by the pre-trial data collection occasion during which baseline measures of primary and secondary outcome variables will be taken. The training will be delivered by experienced teacher trainers as part of the teachers’ regular in-service training. The implementation phase will comprise a one-month period during which teachers will apply their training in their regular PE classes and it is followed by post-trial data collection occurrence. Thereafter, primary and secondary outcome variables will be collected at one-, three-, and six-month follow-up data collection occasions. Teachers allocated to the waitlist control condition receive a 4-h training program in which they will be instructed on how to apply a monitoring system for physical functional capacity in children with special needs [33]. Secondary school teachers (*N* = 29) from 11 secondary schools and their students (*N* = 502) in the city of Jyväskylä in central Finland will be invited to participate in the study.

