## Discussion

School PE is an existing network with considerable potential for the delivery of interventions to promote physical activity to a captive audience of young people. Such interventions are also consistent with PE curricula to promote lifelong physical activity and health. However, relatively few studies have examined the effectiveness of school-based PE interventions in promoting out-of-school physical activity. The goal of the proposed study outlined in this protocol is to address this gap in the literature by testing the effectiveness of a theory-based intervention delivered in PE to promote lower secondary school students’ physical activity outside of school. The intervention will capitalize on the trans-contextual model [6, 10], a motivation model which specifies the processes by which teachers’ support for students’ self-determined or *autonomous* motivation in school translates to their autonomous motivation, beliefs, and intention toward, and actual participation in, physical activity outside of school.

The intervention will make a unique contribution to knowledge in four areas: (i) it will test the effectiveness of a theory-based in-school intervention delivered by PE teachers in promoting lower secondary school students’ physical activity participation outside of school, which has seldom been demonstrated; (ii) it will evaluate how the intervention works in promoting students’ out-of-school physical activity participation through effects of intervention on key constructs from the trans-contextual model; (iii) it will outline the development and implementation of a cost-effective, replicable theory-based teacher training program to train teachers to use autonomy-support techniques in their PE lessons and promote out-of-school physical activity; and (iv) it will evaluate the long-term effectiveness of the intervention in promoting physical activity behaviour through one, three, and six-month post-intervention follow-up of behavioural and theory-based outcomes.

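### At six months no control group unexposed to the programme remains, yet the plan still tests intervention versus control there as a primary occasion

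*Protocol article*

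**What the plan says.** All of this is in the protocol article.

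- **Schedule (Procedure and data collection methods).** "Follow-up data collection occasions are scheduled for one-, three-, and six-months post-trial". The full set of measures is repeated late in follow-up: "All assessments will be completed at the three- and six-month follow up data collection occasions, identical to the post-trial data collection occasion". No exception is made for the wait-list arm.
- **Crossover (same section).** "Immediately after the three-month follow up data collection occasion, the wait-list control group will receive the autonomy-support training program". After that, "Post-trial and one-month follow up assessments will be conducted for teachers and students from this group".
- **Durations (Trial design).** "The teacher-training phase will comprise a two-week, 12-h training program", followed by a one-month implementation phase.
- **Primary outcome (Primary outcome variable).** Out-of-school physical activity is measured "at the pre-trial, post-trial, one-, three and 6 month follow-up data collection occasions".
- **Analysis (Data analysis).** "We will test the model at each of the follow-up time points", with condition coded 1 for intervention and 0 for control. The model variables from the previous occasion are controlled through standardized residual scores, and the psychological variables enter as simultaneous predictors. The Sample size section rests on the same regression at each post-intervention follow-up.
- **Claim (Discussion).** Among the study's contributions, "it will evaluate the long-term effectiveness of the intervention in promoting physical activity behaviour through one, three, and six-month post-intervention follow-up".

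**The concern.** A wait-list design supports a controlled comparison only until the wait-list arm is given the programme. Here that happens straight after three months, but the analysis carries the same intervention-versus-control coding on to six months without recoding, exception or relabelling.

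The six-month coefficient would then be reported as an intervention effect on the primary outcome when it is not one. Any result could mislead. A small or null coefficient might be read as an effect that faded, and a negative one as harm, when either could arise simply because the control schools had been trained. The long-term effectiveness statement would lack a controlled basis beyond three months.

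**Working it through.** The plan gives no expected difference at six months, so there is no figure of its own to reproduce on this point. The check has two parts.

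**1. Timeline, in months after the post-trial occasion**

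Inputs: crossover immediately after month 3 (Procedure); training of two weeks, about 0.5 month, and implementation of one month (Trial design). I assume that the wait-list arm follows the same two phases at the same lengths. Its own post-trial assessment implies this.

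| Event in the wait-list arm | Calculation | Month |
|---|---|---|
| Training starts | stated | 3.0 |
| Training ends | 3.0 + 0.5 | about 3.5 |
| Implementation ends; own post-trial assessment | 3.5 + 1.0 | about 4.5 |
| Own one-month follow-up | 4.5 + 1.0 | about 5.5 |
| Six-month occasion | stated | 6.0 |

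The margin is 6.0 − 4.5 = 1.5 months. Even if training started up to 1.5 months late, the wait-list arm would have completed the programme by the six-month occasion. What can be compared there is one arm 6 months past its implementation phase with another about 1.5 months past its own.

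The text allows two readings of who is measured at six months:
- If both arms are measured, the controls have already been trained and have implemented the programme.
- If the wait-list arm has only its own post-trial and one-month assessments, it has no six-month data.

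Neither reading leaves an unexposed comparator.

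**2. What the condition coefficient would estimate if both arms are measured**

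The occasion before six months is three months, so the model adjusts for values taken just before crossover. As a simplified illustration, leave out the mediators and the clustering and let:
- d = difference between arms at three months, assumed to be maintained in the intervention arm;
- r = within-arm slope of six-month on three-month activity;
- f = fraction of d that the controls gain by six months.

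The raw six-month difference is (1 − f)d. The adjusted coefficient is

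b = (1 − f)d − r·d = (1 − f − r)d.

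The documents give none of d, r or f. With r assumed to be 0.5 or 0.7:

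| f | b at r = 0.5 | b at r = 0.7 |
|---|---|---|
| 0 (no response in controls) | 0.5d | 0.3d |
| 0.5 | 0 | −0.2d |
| 1 (full catch-up) | −0.5d | −0.7d |

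For positive d, the coefficient is negative whenever f exceeds 1 − r. Its sign therefore depends on how strongly the newly trained control schools respond, even when the intervention arm has lost nothing.

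**The case against.** **The timeline figure by group is not shown, and it may exclude the wait-list arm at six months.** That is possible, and it is why one cannot say for certain that a contaminated contrast will be computed. It does not rescue the plan, because without wait-list data at six months the test described under Data analysis cannot be carried out.

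**A statistical analysis plan may settle this.** A separate plan could supply missing detail. Here, however, the protocol itself states both the occasions and the coding, and these conflict with its own schedule.

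**Intention-to-treat keeps schools as randomised.** It does, and an early-versus-delayed contrast at six months is a legitimate randomised comparison. It answers a different question from the hypothesis in the Abstract, which sets the intervention against a control intervention.

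**The long-term claim need not mean a between-arm contrast.** This stands in part. The Discussion also speaks of whether changes are maintained over time, and Data analysis mentions trajectories; both fit a within-arm reading. The text does not say which is meant, while the stated model is a between-arm one.

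**A reader might infer that the six-month contrast is simply biased toward zero, with an expected value of about zero.** That would describe a raw difference with full catch-up in controls. It does not follow from the planned model, which adjusts for three-month values and includes the mediators.

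**A reader might also call the control arm untreated before crossover.** It is not: control teachers receive a 4-h alternative training. The accurate description is unexposed to the autonomy-support programme.

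**Conclusion.** The point holds for the six-month occasion and needs correcting, because a listed primary comparison cannot answer the trial's question as written. By the protocol's own durations, the wait-list arm is fully exposed by about 4.5 months, so no unexposed control exists at 6 months under either reading of the schedule. This rests only on the stated durations and on the wait-list arm following the same two phases.

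No size or direction of bias can be given. The plan states no effect size, and the coefficient depends on the controls' response, the carry-over between occasions and the mediators. It could favour control.

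The point is limited to six months. The post-trial, one-month and three-month comparisons keep a control group unexposed to the programme. A reader might also infer an inflated error rate from testing several occasions. The protocol does not say that any single significant occasion would count as success, and multiplicity rules may sit in an analysis plan that is not shown, so that inference is not part of this finding.

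**What to change.** 1. In Data analysis, limit the randomised intervention-versus-control comparison to post-trial, one month and three months. Make Primary outcome variable and Sample size agree with it.
2. State what the six-month data are for: maintenance within the intervention arm, or a contrast of early versus delayed training labelled as such. For the second, say whether the wait-list arm is measured at the six-month date and which earlier occasion is adjusted for.
3. In the Discussion, limit the controlled long-term effectiveness claim to three months and describe the six-month evidence by its type.
4. Reconcile Procedure and data collection methods with these sections, so that the occasions at which each arm is assessed after crossover are unambiguous.

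The cost is a shorter controlled follow-up claim, three months instead of six. The changes are to wording; data collection stays as planned.
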